## Abstract

**Background:**

The consequences of lifestyle-related disease represent a major burden for the individual as well as for society at large. Individual preventive health checks to the general population have been suggested as a mean to reduce the burden of lifestyle-related diseases, though with mixed evidence on effectiveness. Several systematic reviews, on the other hand, suggest that health checks targeting people at high risk of chronic lifestyle-related diseases may be more effective. The evidence is however very limited. To effectively target people at high risk of lifestyle-related disease, there is a substantial need to advance and implement evidence-based health strategies and interventions that facilitate the identification and management of people at high risk. This paper reports on a non-randomized pilot study carried out to test the acceptability, feasibility and short-term effects of a healthcare intervention in primary care designed to systematically identify persons at risk of developing lifestyle-related disease or who engage in health-risk behavior, and provide targeted and coherent preventive services to these individuals.

**Methods:**

The intervention took place over a three-month period from September 2016 to December 2016. Taking a two-pronged approach, the design included both a joint and a targeted intervention. The former was directed at the entire population, while the latter specifically focused on patients at high risk of a lifestyle-related disease and/or who engage in health-risk behavior. The intervention was facilitated by a digital support system. The evaluation of the pilot will comprise both quantitative and qualitative research methods. All outcome measures are based on validated instruments and aim to provide results pertaining to intervention acceptability, feasibility, and short-term effects.

**Discussion:**

This pilot study will provide a solid empirical base from which to plan and implement a full-scale randomized study with the central aim of determining the efficacy of a preventive health intervention.

**Trial registration:**

Registered at Clinical Trial Gov (Unique Protocol ID: TOFpilot2016). Registered 29 April 2016. The study adheres to the SPIRIT guidelines.

**Electronic supplementary material:**

The online version of this article (10.1186/s12875-018-0820-8) contains supplementary material, which is available to authorized users.

## Background

In this paper we report on a non-randomized pilot study examining the efficacy of a preventive healthcare intervention. The intervention has been designed to systematically identify patients at high risk of developing lifestyle-related disease, and provide targeted and coherent preventive services to these individuals [1].

Lifestyle-related disease refers to health conditions that are predominantly caused by health-risk behaviors, such as poor diet, smoking, high consumption of alcohol, or lack of exercise. The consequences of lifestyle-related disease represent a major challenge for the individual as well as for society at large [2]. In Denmark, people who smoke tobacco, consume excessive amounts of alcohol, and have a sedentary lifestyle are nearly seven times as likely to die from lifestyle-related diseases than physically active non-smokers with a moderate intake of alcohol [3]. It is estimated that 80% of cardio-vascular disease (CVD), type 2-diabetes mellitus (T2DM), and chronic obstructive pulmonary disease (COPD), and 40% of all cancers may be averted by maintaining healthy dietary habits, regularly exercising, and refraining from smoking [4]. Indeed, preventable lifestyle-related diseases account for approximately 50 to 60% of all hospital admissions [5]. It is expected that increasing rates of obesity and physical inactivity will lead to a surge in the number of patients with lifestyle-related diseases in the decades to come [6–8]. In light of these trends, there is a substantial need to advance and implement evidence-based health strategies and interventions that facilitate the identification and management of people at risk of developing these diseases [9].

Disease prevention is a central task in general practice in Denmark and the Nordic countries [10]. Two recent systematic reviews of general practice health checks suggest that people at high risk of chronic disease may benefit from targeted preventive health checks [11, 12]. Indeed, targeted, or selective, preventive healthcare is a generally accepted and well-integrated part of healthcare systems worldwide (e.g. treatment of hypertension and hyperlipidemia). Other studies, however, suggest that systematic screening of the general population does not improve clinical endpoints above and beyond those associated with opportunistic screening. These studies indicate that, at a population level, systematic screening of the general population does more harm than good [13–15]. Overall, however, the evidence on targeted and systematic screening of chronic disease is very limited, possibly providing an explanation for the apparent contradictions in the literature. To this end, projects in the Netherlands and Great Britain are currently underway, testing different approaches to targeted and systematic intervention in general practice [16, 17].

There is an even greater lack of evidence when it comes to targeted preventive interventions that comprise both general practice and community health services. In such an approach the general practitioner (GP) targets patients at high risk for lifestyle-related diseases and engages in risk-management of biomarkers and disease with behavior change and pharmaceutical interventions when needed. Community health services, on the other hand, focus primarily on the prevention of health-risk behaviors - including tobacco use, poor diet, excessive alcohol consumption, and sedentary lifestyles - and provide behavior-change interventions such as smoking cessation assistance and dietary advice. Danish studies suggest a potential to enhance the collaboration and cohesiveness of the various components that comprise the preventive healthcare services in the Danish primary care system – especially between GPs and community health services [18, 19]. Outside of the Danish context, the benefits of a more unified and coherent healthcare service have also been advanced in peer-reviewed studies [20, 21]. However, effectiveness studies of a unified approach, such as that described above, seem to be lacking.

In 2012, we carried out a feasibility study, testing a novel approach to population-based risk stratification at four Danish GP clinics [22]. The intervention combined lifestyle survey data with health record information in order to identify presumably healthy individuals who nonetheless were at high risk of developing lifestyle-related diseases. These individuals were then offered a health check at their GP for a more definitive assessment of their general health as well as their risk of developing lifestyle-related diseases. Results indicated that this approach to preventive action was indeed feasible, and thus ultimately inspired the development of a large randomized study, the present TOF-project (TOF is a Danish acronym for Early Detection and Prevention). The principal aim of the upcoming TOF-project is to examine the efficacy of a preventive healthcare intervention that systematically identifies individuals at high risk of lifestyle-related disease, and provides targeted and coherent preventive services. We expect that significant changes in the targeting and systematization of disease prevention in the Danish primary care sector, including earlier detection and more coherent preventive services, will diminish the individual and societal burden of chronic disease. Due to the complexity of the TOF intervention, and the relatively high number of stakeholders, a pilot study needs to be conducted before full-scale implementation and evaluation [23]. The aim of the pilot study is to test the acceptability, feasibility, and short-term effects of a selective preventive program, designed to systematically help patients evaluate their individual risk of lifestyle-related disease. The program also offers targeted and coordinated preventive services in the primary healthcare sector.

## Methods

The pilot study was designed as a population based non-randomized study in the Region of Southern Denmark, comprising 22 municipalities, 787 GPs, and a general population of 1,2 million. The Danish health care system is a tax-based system comprising three levels: A national level responsible for, among other things, public health, planning, and patient safety; a regional level responsible for the hospitals and the primary care sector; and a municipal level responsible for primary prevention, rehabilitation, and patient education. General practice and the municipalities have shared responsibility for preventive services aimed at the individual. Specifically, GPs assess patient health and implement disease-specific secondary prevention. The municipalities, however, are tasked with primary prevention such as smoking cessation, alcohol treatment, and other lifestyle related services. GPs are organized in clinics with an average of two GPs per clinic. While most clinics comprise a single GP, some have up to ten. Almost all Danish citizens (98%) are registered with a GP [24, 25]. Each GP has an average of 1600 registered patients.

### Recruitment

The pilot study targets adults born between year 1957 and 1986. All 22 municipalities in the Region of Southern Denmark were invited to participate in TOF. Ten municipalities (Esbjerg, Haderslev, Varde, Sønderborg, Aabenraa, Middelfart, Kerteminde, Nyborg, Svendborg, Langeland) submitted expressions of interest to participate in the study, and were approved for participation by the Regional Council. Two of the municipalities (Haderslev and Varde) volunteered to participate in the pilot study.

The municipalities of Haderslev and Varde comprise 55,971 and 50,110 citizens, and 37 and 29 GPs, respectively. All GPs from each municipality were invited to an information meeting before being formally invited to participate in the pilot study. The invitation was followed up with telephone calls to the individual GP clinics. All patients were invited at baseline, and the intervention was taken up by the patients at their own convenience during the intervention period. See Additional file 1 for a more detailed project flow showing the recruitment, intervention and evaluation phases.

### Organization and development of the intervention

The intervention was planned during a two-year combined effort involving all stakeholders. End users were involved in the design of the intervention, including patients, GPs, and municipal health professionals. A group of seven GPs developed the targeted intervention at a general practice level during five workshops. Similarly, a group of 10 municipal health workers, one from each of the participating municipalities, developed the targeted intervention at a municipal level during 10 workshops. The workshops lasted between 2 h and 2 days. A digital support system was created and tested by user populations, including patients, non-government patient organizations, GPs, and municipal health professionals.

A steering committee was established at the start of the project, consisting of managers or board members from the Region of Southern Denmark (project owner), The Organization of General Practitioners in Denmark (PLO), the 10 participating municipalities, the Research Unit for General Practice at the University of Southern Denmark (FEA), and the Danish Quality Unit for General Practice (DAK-E). The chair of the committee is the health director from the Region of Southern Denmark. A research committee with participation from the steering committee chair and the primary investigator has been established. A mission statement has been approved by the steering committee and an agreement of co-operation has been signed between the Region of Southern Denmark and the University of Southern Denmark. The agreement states that the University of Southern Denmark holds all rights, intellectual as well as judicial, to the research data, and that the Region of Southern Denmark has no right to oppose publication of results. The research committee approves all access to research data from affiliated researchers.

Prior to study commencement, all enrolled GPs, practice nurses (PN), and health professionals from the municipalities were invited to a joint three-hour training course (August 2016). The course focused on the assigned intervention activities and tasks both within the GP clinics and the municipality respectively, and between GPs and the municipality.

### Invitation and consent

The source population received an invitation to participate, sent on behalf of the GP and the municipality to the individual’s digital mailbox. All permanent residents in Denmark are obligated to have a digital mailbox, which is essentially a digital mail-system provided by the government for secure and direct communication between individuals and public authorities and other trusted organizations (e.g. banks and insurance companies) [26]. People may opt out of the digital mail system, citing low IT-literacy (usually elderly persons), cognitive impairment, or other complicating factors. To enroll in the study, individuals were asked to follow a link in the invitation to a digital support system protected by a two-phased NemID password [27]. NemID is a password system providing an exact identification of the user. This system is utilized by Danish public and non-public institutions to provide secure access to personal information, such as health and financial data. Through digital mail and NemID, we were able to reach and identify 97% of the target population. In April 2016, participants received an invitation with an embedded hyperlink to a digital consent form on a secure webpage in their digital mailbox. The consent form outlined study participation and disclosure of data from the GPs electronic patient record (EPR) and was supplemented with short videos describing the purpose of the study and the intervention. Participants were asked to read the information and electronically sign the consent form. Two reminders were sent after one and 2 weeks if participants failed to sign the form. Enrollment closed after 6 weeks. At this time, information on relevant diagnosis (International Classification of Primary Care (ICPC-2) codes) and prescribed medicine (Anatomical Therapeutic Chemical Classification (ATC) codes incl. Text fields with indication for treatment) were collected from the GPs EPR system (See Table 1 for the ICPC-2 codes and ATC codes that were accessed based on the consent). Five months after consent (September 2016), participants received another digital invitation in the digital mailbox, this time to fill in a questionnaire and access a personal health profile. Participants could opt-out at any time during the intervention period by clicking an “opt-out” button on the digital support system.

**Table 1 Tab1:** The 5As model

Assess	Initial questionnaire-derived assessment of the patients’ health / risk profile for the purpose of identifying patients in need of health-risk behavior change Subsequent health examination at the GP to confirm or disprove estimated risk of disease
Advice	Counseling, based on the patient’s symptoms / risk profile. The patient’s values and attitudes can usefully be involved
Agree	Active involvement of the patient in connection with goal setting regarding health-risk behavior change
Assist	Joint development of plan for health-risk behavior change
Arrange follow-up	Planning of the next steps at the GP or other (e.g. the municipality)

### Intervention

The duration of the intervention was 3 months and took place between September 2016 and December 2016. The intervention comprised a two-pronged approach: [1] a joint intervention applied to the entire sample, regardless of whether the participants were healthy, at risk, or already in treatment for T2DM, COPD, CVD, hypercholesterolemia or hypertension [2] a targeted intervention that was offered only to participants who presumably would benefit from either further examinations at the GP (high risk), or from receiving community health services, such as smoking cessation, dietary advice, or physical activity (health-risk behavior).

*The joint intervention consisted of:*
Stratification to one of four risk groups. Stratification to a specific risk group was determined by use of risk algorithms and EPR informationA digital support system with user interfaces for all users, including the patient, the GP, and the municipal health professionalAn individual health profile

*The targeted intervention consisted of:*
A focused clinical examination and a subsequent health dialogue with a GP (targeting patients at high risk), *and / or*A short telephone-based health dialogue with a municipal health professional. For patients with limited capability to care for their own health, this initial talk could be followed up with a subsequent face-to-face health dialogue (targeting patients with health-risk behavior)

For all present intents and purposes, the term *health dialogue* refers to a consultation that includes the elements of the 5As model (see Table 1) and the techniques used in motivational interviewing [28, 29].

### The joint intervention

All participants gained access to the digital support system and were invited to fill in a questionnaire. The participant questionnaire contained 15 items on height, weight, self-perceived health status, family history of lifestyle-related diseases, COPD related symptoms, smoking status, leisure activity level, alcohol consumption, diet, and osteoarthritis risk factors. Questions about family history of diabetes and leisure activity level were taken from the Danish Diabetes Risk model [30]. Similarly, questions on COPD-related symptoms and smoking status were derived from the COPD-PS screener [31] and the Heartscore BMI score [32]. Items tapping dietary habits were from the Swedish National Guidelines on Disease Prevention [33]. The questionnaire took approximately 5 min to complete.

Based on the questionnaire and information from the individual EPR, participants were stratified into four distinct risk groups:*Group 1* – Participants with a pre-existing diagnosis and/or in current treatment for a lifestyle-related disease.*Group 2* – Participants at high risk of developing lifestyle-related disease, and thus eligible for the offer of a targeted intervention at the GP.*Group 3* – Participants engaging in health-risk behavior, and thus eligible for the offer of a targeted intervention at the municipality.*Group 4* – Participants with a healthy lifestyle and no need for further intervention.

### Stratification to group 1

EPR data was collected via certified EPR-suppliers. We used International Classification of Primary Care-2 codes (ICPC-2) registered by the GP and/or Anatomical Therapeutic Chemical Classification **(**ATC) codes for prescribed medicine within the past 2 years, together with the indication for prescribing the medicine, to identify Group 1 participants (see Table 2).

**Table 2 Tab2:** Criteria for identification of participants with a pre-existing diagnosis and/or in current treatment for a lifestyle-related disease

Diagnosis	Diagnostic code(s) (ICPC-2)		ATC therapeutic code(s) for prescribed medicine and indicative texts for the prescription^a^
Hypertension	K86, K87	or	C0 *BT*, *bt*, *Bt*, *ypert*, *ldot*, *LODTR*, *lotr*, *lodptr*, *blodtryk* *bl. trykket*, *lodrtr*^b^
Hyperlipidemia	T93	or	C10 *kolesterol*
COPD	R95	or	R03AC18 (indacaterol), R03AC19 (Olodaterol), R03AL03 (vilanterol), R03AL04 (Indacaterol+Glycopyrroniumbromide), R03AL05 (Formoterol+Aclidiniumbromide) R03BB04 (tiotropium bromide), R03BB05 (Aclidiniumbromide), R03BB06 (Glycopyrroniumbromide)*obstruktiv*, *KOL*
T2DM	T90	or	A10(diabetes medicine) *sukkersyge*, *diabetes*
CVD	K74, K76^c^		

^a^The indicative text is in Danish and has not been translated as some indicative texts are only parts of the entire word and as such not translatable

^b^The reason for the large number of indicative text is misspellings by the GP when indicating the purpose of the prescription

^c^Diagnostic codes for ischemic heart diseases are transferred to the GP’s EPR system when the patients are discharged from the hospital following an angina or a stroke. ATC codes for prescribed medicine will not provide further information

Given the pre-existing diagnosis and/or treatment, Group 1 was excluded from the subsequent risk estimation and stratification into Group 2, 3, and 4.

### Stratification to group 2

Next, participants at risk of lifestyle-related disease were identified using three validated risk scores: the Chronic Obstructive Pulmonary Disease Population Screener (COPD-PS), the Danish Diabetes Risk model, and a modified Heartscore BMI score [30–32]. The COPD-PS uses an algorithm accounting for age, lifetime use of cigarettes, and smoking-related symptoms to identify at-risk patients who may benefit from a spirometry to test for COPD (Table 3) [31]. The Danish Diabetes Risk score is based on an algorithm that incorporates age, sex, BMI, known hypertension, leisure activity level, and family history of diabetes (Table 4) [30]. The modified Heartscore BMI score accounts for age, sex, body mass index (BMI), and smoking status (Table 5) [32].

**Table 3 Tab3:** Algorithm used for risk assessment of COPD

Characteristic		Score
During the past 4 weeks, how much of the time did you feel short of breath during every day activities? (e.g. Strolling, light gardening, cleaning, shopping etc.)	None of the time	0
	A little of the time	0
	Some of the time	1
	Most of the time	2
	All of the time	2
Do you ever cough up any “stuff,” such as mucus or phlegm?	No, never	0
	Only when I have a cold, pneumonia or sore throat	0
	Yes a few days a month	1
	Yes most days a week	1
	Yes every day	2
Please select the answer that best describes you in the past 12 months. I do less than I used to because of my breathing problems.	Strongly disagree	0
	Disagree	0
	Unsure	0
	Agree	1
	Strongly agree	2
Have you smoked at least 100 cigarettes in your ENTIRE LIFE?	Yes	2
	No	0
Age	35–49 years	0
	50–59 years	1
	60–69 years	2
	+ 70 years	2

Cut off value: ≥5

**Table 4 Tab4:** Algorithm used for risk assessment of T2DM

Characteristic	Score
Sex	
Male	1
Female	0
Age	
40–44 years	0
45–49 years	1
50–54 years	2
55–59 years	3
60–69 years	4
BMI	
25–30 kg/m^2^	1
> 30 kg/m^2^	2
Known hypertension	
Yes	2
No	0
Primary recreational activity level during the past year:	
Participating in sports competitions or hard exercise several times a week	0
Active with sports at least three times a week or regularly perform heavy house or garden work	0
Strolling, cycling or other light exercise at least 4 h a week (including Sunday walks, light gardening and cycling/walking to work)	1
Reading, watching television or other sedentary jobs	1
Family history of diabetes (Family includes grandparents, parents, sibling and children):	
No family member with diabetes before the age of 70	0
One family member with diabetes before the age of 70	1
More than one family member with diabetes before the age of 70	2
Having had diabetes including gestational diabetes	
Yes	2
No	0

Cut off value: ≥5

**Table 5 Tab5:** Algorithms used for risk assessment of CVD

Age	BMI	Daily smoker
Female		
> 50 years	> 40 kg/m^2^	+
> 55 years	> 40 kg/m^2^	–
> 58 years	35–40 kg/m^2^	+
Male		
> 49 years	> 40 kg/m^2^	+
> 55 years	> 40 kg/m^2^	–
> 50 years	35–40 kg/m^2^	+
> 55 years	35–40 kg/m^2^	–
> 52 years	30–35 kg/m^2^	+
> 56 years	25–30 kg/m^2^	+

Consistent with the criteria of the four distinct stratification groups defined above, participants were categorized into Group 2 when one or more of the risk assessment algorithms indicated high likelihood of developing lifestyle-related disease (see Tables 3, 4 and 5).

### Stratification to group 3 and 4

Finally, participants engaging in health-risk behavior with one or more risk factors were categorized in Group 3 (Group 3). Health-risk behavior was defined by the presence of at least one of the following behaviors: smoking tobacco on a daily basis, consuming more than 14/21 (male/female) standard units of alcohol per week, sustaining an unhealthy diet (diet score ≤ 4 on a 12-point score drawn from the Swedish National Guidelines on Disease Prevention) [4], maintaining a BMI ≥ 35, and/or engaging in a generally sedentary lifestyle. Lastly, participants with no lifestyle-related disease or risk thereof were stratified into Group 4.

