### Personal health profile

Based on results of the stratification process, each patient received a personal health profile on the digital support system. The purpose of the health profile was to encourage patients to change their health-risk behavior and follow the tailored advice provided by the system. Patients who were at increased risk of developing a lifestyle-related disease (Group 2) were advised to consult their GP for further examination and advice. Similarly, patients engaging in health-risk behavior (Group 3) were offered lifestyle counseling, or lifestyle courses from the municipality health services. By definition, Group 4 patients lead a relatively healthy life with no need for health-risk behavior change. Group 1 patients were advised to continue their treatment and use the information provided to change health-risk behavior.

The personal health profile included individualized information on current health-risk behavior and risk of disease. The information was tailored based on the questionnaire, the information from the EPR, and the risk scores on COPD, T2DM, and CVD. It also included general health information and information about preventive health services concerning smoking, diet, exercise, and alcohol consumption. This information was provided by the municipality, the Region of Southern Denmark, or national health services, and targeted the individual (e.g. via links to apps and webpages) based on his/her specific health-risk behavior.

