#### The intervention at the municipal level

The intervention at the municipal level was offered to patients exhibiting health-risk behavior (Group 3) and consisted of a short telephone consultation with a health professional – for example a nurse, a dietician, or a physiotherapist. A subsequent face-to-face health dialogue was offered to patients who were deemed to potentially benefit from more extensive support. Group 3 patients requested the intervention on the digital support system by filling in a short form and sending it by e-mail to the municipality. A municipal health professional would then call the patient within the following week. Similar to the GP intervention, the intervention at the municipal level was thus also determined by patient motivation and capabilities as well as the extent to which the content of the personal health profile motivated the patient to take action. Immediately after the intervention, a participation form was sent to the municipality. Patients could prepare for the upcoming call from a municipal health professional in the same way as Group 2 patients prepared for the health dialogue – that is, by answering a short questionnaire. Ultimately, a prevention plan, including concrete details on its execution, was developed based on the telephone consultation and the face-to-face health dialogue. The prevention plan was registered by the municipal health professional and presented on the user interfaces of both the municipality and the patient.

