### Data collection and analysis

#### Evaluation outcomes

Evaluation of the study will be carried out using quantitative as well as qualitative research methods (Table 6). All outcome measures are based on validated instruments and aim to provide results pertaining to intervention acceptability, feasibility, and short-term effects. In addition, outcomes related to other associated topics will be included. The specific instruments used will be described in detail in later publications.

**Table 6 Tab6:** Outcomes

Outcome	Data input
Change in proportion of patients at increased risk of lifestyle related disease from baseline to the 12 weeks follow up	Questionnaire at baseline (Q2) and end of study period (Q6 and Q7). Risk of lifestyle related disease is based on the algorithms previously described in the methods section and in Tables 3, 4 and 5
Determinants of participation and non-participation	Questionnaire at baseline (Q2). Participants and non-participants will be compared with regard to socio-demographic characteristics, morbidity and contextual characteristics
Evaluation of the digital support system with focus on design, usability and effect of the decision support system	Focus group interviews before study start comprising 6 GPs, 6 practice staff members, 6 municipality staff members, 6–8 patients and representatives from 6 to 8 stakeholder organizations, respectively
	Qualitative interviews with 8–10 patients before and after the health dialogue at the GP, and qualitative interviews with 6–8 GPs after health dialogues, focusing on the experienced usefulness of the digital support system
	Questionnaire to all participating patients immediately after signing the consent form (Q1) and after receiving the health profile (Q3 and Q4) and to all participating GPs and municipality staff members following each study related patient encounter (Q8-Q13)
Process evaluation focusing on the intervention in general practice and the municipality	Participant observation of 10–15 health dialogues in different general practices, followed by qualitative interviews with the participating patients, GPs and practice staff
	Focus group interviews with 6–8 municipality staff members involved in the study and interviews with 10–15 patients who have attended a health dialogue in the municipality
	Questionnaire to all participating GPs, practice staff members and municipality staff members following each study related patient encounter (Q8-Q13)

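### The Group 3 alcohol limit is printed as 14 units per week for men and 21 for women, apparently with the sex labels swapped

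*Protocol article*

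**What the plan says.** The protocol article sorts participants into four groups in a fixed order.

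- **Group 1** (existing diagnosis or treatment) is set from record data and then leaves the process: "Group 1 was excluded from the subsequent risk estimation and stratification into Group 2, 3, and 4".
- **Group 2** (high risk) comes next: "participants were categorized into Group 2 when one or more of the risk assessment algorithms indicated high likelihood of developing lifestyle-related disease". The algorithms are those in Tables 3, 4 and 5.
- **Group 3** (health-risk behavior) is taken from the rest. One behavior is enough: "Health-risk behavior was defined by the presence of at least one of the following behaviors". The list has daily smoking, alcohol, a diet score of 4 or less, BMI of 35 or more, and a sedentary lifestyle. The alcohol item reads "consuming more than 14/21 (male/female) standard units of alcohol per week".
- **Group 4** is what remains: "Participants with a healthy lifestyle and no need for further intervention".

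The group decides the offer. Under the heading on the personal health profile, "patients engaging in health-risk behavior (Group 3) were offered lifestyle counseling, or lifestyle courses from the municipality health services".

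For the primary health-related outcome, Table 6 states: "Risk of lifestyle related disease is based on the algorithms previously described in the methods section and in Tables 3, 4 and 5".

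**The concern.** The printed order gives men the stricter limit, 14 units against 21 for women. Sex-specific weekly alcohol limits are generally lower for women, so the reverse order would need a reason. The article gives none, attaches no source to the alcohol limit, and does not restate it anywhere that would settle the order.

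This is an operative threshold. A participant with no other listed behavior is moved between Group 3 and Group 4 by this number alone, and with that gains or loses the municipal offer. If the digital system ran the printed rule, some women whose drinking should have triggered the offer did not get it, and some men got it needlessly. If only the article is wrong, the risk is that the printed rule is copied into the full-scale trial that this pilot is meant to prepare.

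**Working it through.** The limit is a stated criterion, so there is no derived figure to reproduce. The check compares the two possible rules and then follows the difference through the group order.

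**1. Where the rules differ.** Printed rule: men above 14, women above 21. Swapped rule: men above 21, women above 14. The limits are 21 − 14 = 7 units apart.

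| Units per week | Men, printed | Men, swapped | Women, printed | Women, swapped |
|---|---|---|---|---|
| 14 or fewer | no | no | no | no |
| 15–21 | **flagged** | **no** | **no** | **flagged** |
| 22 or more | flagged | flagged | flagged | flagged |

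In whole units the rules disagree only at 15–21, and in opposite directions by sex.

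**2. Who changes group.** Being in that band is not enough. The person must also:

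- be outside Group 1, which is removed first;
- be outside Group 2, which depends on Tables 3–5, none of which has an alcohol item;
- have none of the other four listed behaviors, since any of them gives Group 3 whatever the alcohol intake.

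Only people meeting all these conditions move between Group 3 and Group 4.

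**3. Primary health-related outcome.** Its classification uses Tables 3–5 only, so alcohol does not enter it. The limit plays no part in the sample size calculation either.

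**4. How many people.** The article gives no drinking distribution, no Group 1 share and no sex split, so the number cannot be derived. A ceiling follows from the planning figures: a target population of 9,400 (register data section), and 60% consent, 75% of consenters receiving a profile and 12% in Group 2 (sample size section).

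The 12% is applied here to people with a profile. That reading roughly reproduces the article's own target of four health checks per GP, using its 35% attendance: 200 × 0.60 × 0.75 × 0.12 × 0.35 = 3.78.

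- Expected profiles: 9,400 × 0.60 × 0.75 = 4,230
- Expected Group 2: 4,230 × 0.12 = 507.6, about 508
- Groups 1, 3 and 4 together: 4,230 − 508 = 3,722
- 1% of these: 3,722 × 0.01 = about 37

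Group 1 is still inside the 3,722, so fewer people than that reach the alcohol rule. Each 1% of them who drink 15–21 units and have no other listed behavior is therefore at most about 37 people. The 1% is only a unit of scale, not an estimate.

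**The case against.** The strongest reply is that the swap cannot be proved from the article. It holds no second alcohol limit to contradict the printed one, and the case rests on general knowledge that limits are lower for women. **This stands**, and it is why the swap is called an inference here.

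It can also be said that a label slip in a condensed article is more likely than a fault in the live system. GPs and municipal health workers developed the targeted intervention in workshops and took part in the iterative development of the digital system, and might have noticed a reversed limit. **This is plausible but does not settle the matter.** Nothing in the article shows which rule ran, and one check would answer it.

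The harm is limited even in the worst case. The municipal contact was a short telephone consultation that the participant had to request. A woman left in Group 4 still received a personal health profile, and profiles covered preventive services on alcohol. **This stands and bounds the size.** She would still have lost the targeted offer.

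The headcount says little, because the ceiling includes Group 1 and everyone already in Group 3 for another reason. **This also stands**; the figure is an upper bound only.

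Finally, municipal staff rate the quality of the stratification (Q12 and Q13), and the article promises a thorough assessment of problems before the full-scale study. **This helps only in part.** Women wrongly left in Group 4 were not offered the municipal contact that prompts those questionnaires, and a general assessment need not catch a reversed label.

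**Conclusion.** The concern holds. The printed threshold gives women a limit 7 units per week above that for men without explanation, and it decides a pathway on its own for people with no other listed behavior. It should be fixed, but its reach is narrow: 15–21 units per week, outside Groups 1 and 2, and no other listed behavior. The number affected is unknown. Under the planning assumptions it is at most about 37 people for each 1% of those reaching the rule, and it is zero if the system already ran the lower limit for women. The primary health-related outcome's classification and the sample size are untouched.

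Two assumptions carry the conclusion: that the intended limit was lower for women, which rests on general convention, and, for any misassignment, that the digital system applied the limit as printed.

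**What to change.** 1. Check the alcohol rule programmed in the digital support system.
2. Correct the text to 14/21 (female/male), or state the reason and source if the printed order was intended.
3. Carry the confirmed rule into the full-scale trial.
4. If the system ran the reversed limits, report how many participants were misassigned, by sex. Keep the group actually delivered for analyses of uptake and process, because that is the offer people received. Apply the corrected limit to the stored Q2, Q6 and Q7 answers only for descriptive figures on risk drinking or for a sensitivity grouping.

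The cost is one check and a one-line correction. The count in step 4 is needed only if the reversed rule was live. It uses alcohol answers already collected, provided they were stored in enough detail to separate the 15–21 unit band, which the article does not say.
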